### Interim analyses

The objective of interim analyses will be to determine if there exist profiles of patients with specific characteristics, to assess if the interventions act differently according to subgroup. We hypothesize a subdivision of patients according to the presence of a more cognitive or psychological profile. For this Latent Profile Analysis (LPA), the z-standardized mean scale scores of the following variables will be entered in the model: composite scores for memory, attention and executive performance, global score at OCQ and M-FIS. All this continuous variables will be used If the presence of these two sub-groups is confirmed, we will next assess if they differ on primary outcomes (complaints at BRIEF and MMQ scales), quality of life (ISQV), medical variables (length of potential hospitalization; presence and duration of ventilation; presence of neurological symptoms at acute phase time since infection), presence/absence of antecedent psychological difficulties, age and sex.

### Methods for additional analyses (e.g. subgroup analyses)

Analyses will be conducted to identify trajectories of participants according to their baseline characteristics (i.e., subgroup identified with the cluster analysis) and the allocated intervention. To explore the effects of the intervention on the two primary outcome measures according to the baseline participant characteristics (profile corresponding to cognitive or psychological difficulties), the same analysis will be performed as for primary outcomes (linear mixed models, see (Statistical methods for primary and secondary outcomes), with inclusion of the subgroup as a supplementary fixed variable.

Analyses will be conducted to identify individual trajectories, in the different cognitive domains and for primary outcome, to identify which variable predict long-term cognitive sequelae. Our analyses will include latent growth curve modelling techniques that use repeated measures to estimate trajectories.

### Methods in analysis to handle protocol non-adherence and any statistical methods to handle missing data

In the ITT analysis, we will measure our primary and key secondary outcomes by patient report in the last assessment. For the PP analysis, the proposed linear mixed model allows missing values at certain time points. The missing value assumption of the model is Missing At Random which means that missing values can only be dependent on the observed responses which seems a reasonable assumption in this case. Missing data should be kept at minimum by applying the following rules: We will check completion of questionnaires at the end of the testing session and ask the participant to try to complete missing information.

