#### Primary outcome

The primary outcome is a subjective report of difficulties experienced by patients in daily life at two months post-intervention measured via two questionnaires.

The Behavioral Rating Inventory of Executive Function (BRIEF) is a validated questionnaire assessing the main cognitive complaints of the patients (e.g., attention, concentration, disorganization,). It measures the impact of difficulties in daily life and has two indexes (Behavioral Regulation, BRI; Metacognition, MI) and an overall score (Global Executive Composite, GEC). The BRIEF’s reliability is high; Cronbach’s alphas for the BRI and MI have been found to be 0.94 and 0.96, respectively [39].

The Multifactorial Memory Questionnaire (MMQ) is a validated questionnaire measuring affects related to memory abilities, frequency of forgetfulness in different situations, and strategies used in everyday life to cope with memory difficulties. The scores proved to be reliable (Cronbach's α for the subscales ranged from 0.79 to 0.88) [40].

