#### Secondary outcome 

BRIEF and MMQ will also be administered 8 months after intervention. Other secondary outcomes at 2- and 8-months post-intervention are [1] quality of life; [2] the presence of objective cognitive difficulties, assessed by neuropsychological tasks; [3] fatigue level and sleep quality; [4] psychological distress; [5] work productivity and activity impairment.

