### Data collection and management

#### Plans for assessment and collection of outcomes

All tests and questionnaires are administered by a trained psychologist specialized in neuropsychology. The primary outcome is administered via a computerized questionnaire system in the eCRF (Castor). MMQ and BRIEF (primary outcome) will be remotely administered again after a 2-week interval to take account of fluctuating difficulties.

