#### Primary outcome analysis

Primary outcome will be first analyzed on an intention-to-treat (ITT) basis, including all patients as originally allocated after randomisation. For missing information due to patient drop-out, we will rely on the linear mixed model and consider the baseline data as part of the outcome matrix. We will also perform a per-protocol (PP) sensitivity analysis including only those patients who completed the treatment originally allocated.

Analyses should be considered as hypotheses generating. To explore the effects of the intervention type on the two primary outcome measures, the results will be compared using linear mixed models. More precisely, the moment of the measure (baseline and immediate follow-up), the intervention (nested within the centers), the centers and the interaction of these factors will be considered as fixed factors. A nested random intercepts and slopes for each participant within the centers will be implemented. Age groups, educational level, objective Z-score (Z-score from 0 to -0.50; -0.51 to -1, etc.) and gender will also be included in the model as stratification factors. Following the linear mixed model, linear contrast will be performed between the two levels of the intervention variable on the first follow-up measure (T1) to explicitly compare the potential benefit of the intervention. Bonferroni adjustment will be performed to correct for multiple testing, more precisely 2 tests (the number of primary measures), and p-value < 0.025 will be considered as statistically significant. 95% CI and standardized effect sizes (SES) from the null model will be calculated. The following convention will be used to interpret effect size: small 0.2–0.49, moderate 0.5–0.79, large ≥ 0.8. As a Proof-of-Concept (POC) study, estimation will be focused on ES but will include p-values as help in interpreting the data.

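### The missing-data section takes the ITT outcome at an undefined last assessment, which conflicts with the two-month (T1) mixed-model analysis fixed elsewhere in the protocol article

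*Protocol article*

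**What the plan says.** All places are in the protocol article.

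- **Primary outcome** section, on timing: "The primary outcome is a subjective report of difficulties experienced by patients in daily life at two months post-intervention measured via two questionnaires". These are BRIEF and MMQ.
- **Secondary outcome:** "BRIEF and MMQ will also be administered 8 months after intervention". The 8-month scores are therefore secondary.
- **Primary outcome analysis:** "Primary outcome will be first analyzed on an intention-to-treat (ITT) basis, including all patients as originally allocated after randomisation". On drop-out: "For missing information due to patient drop-out, we will rely on the linear mixed model", with baseline kept as part of the outcome. The moments in the model are baseline and immediate follow-up, and the arms are contrasted at the first follow-up (T1). The per-protocol analysis is a sensitivity analysis in patients who completed their allocated treatment.
- **Secondary outcome analysis:** the same models are applied to the other outcomes at T1 and T2.
- **Methods to handle protocol non-adherence and missing data:** "In the ITT analysis, we will measure our primary and key secondary outcomes by patient report in the last assessment". The next sentence reads: "For the PP analysis, the proposed linear mixed model allows missing values at certain time points". The missing-at-random assumption of the model is then stated.
- **Plans for assessment and collection of outcomes:** "MMQ and BRIEF (primary outcome) will be remotely administered again after a 2-week interval to take account of fluctuating difficulties".

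**The concern.** The section that governs missing data gives a different rule for the same primary analysis from the section that defines it. It takes the ITT outcome at an assessment that it does not define. It also brings in the mixed model while speaking of the per-protocol set, although the primary analysis section had already given that model to the ITT analysis.

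Two things are at stake. The first is the time point: on the literal reading, the ITT endpoint moves from two months to eight. The second is the handling of missing scores: in a section about missing data, *last assessment* can be taken as the last score available. That is a different estimator from a likelihood-based model under missing at random. The article says that interpretation will centre on effect sizes, and both of these choices act directly on the effect size.

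**Working it through.** **1. Readings of the phrase.** Assessments are at baseline, 2 months and 8 months after treatment, and BRIEF and MMQ are repeated remotely after two weeks.

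| Reading of *last assessment* | Agrees with the two-month outcome and T1 contrast? |
|---|---|
| 8-month visit (literal) | No: this is a secondary time point |
| Last available score | No: the primary section uses the mixed model for drop-out |
| Two-week repeat of BRIEF and MMQ | Unclear: its role in the T1 score is not stated |
| T1, as the later of the two moments in the primary model | Yes |

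Only the last reading clearly agrees with the rest of the article, and the text does not select it.

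**2. The plan's own design figure.** Inputs from the Sample size section: N = 130, alpha = 0.025, power = 0.80, intra-subject correlation 0.5, two groups. The number of measurements m is not stated. For the within-between interaction, the noncentrality is f² × N × m / (1 − 0.5), with df1 = m − 1 and df2 = 128 × (m − 1).

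- m = 2: detectable f = 0.1365, and power at f = 0.137 is 0.803 (noncentrality 0.137² × 130 × 2 / 0.5 = 9.76).
- m = 3: detectable f = 0.122, and power at f = 0.137 is 0.893.

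The stated f = 0.137 is reproduced with two measurements. This agrees with a model on baseline and one follow-up. It does not by itself show which follow-up was meant. In a two-by-two layout the difference in change is 4 × 0.137 = 0.548 SD, which is the source of the 0.55 SD used below.

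**3. Illustration: baseline carried forward to T1.** The article gives no drop-out rate, so these rates are assumptions, equal in both arms. The expected estimate is effect × (1 − proportion without T1).

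- 10% missing: 0.55 × 0.90 = 0.495, about 0.50 SD
- 20% missing: 0.55 × 0.80 = 0.44 SD
- 30% missing: 0.55 × 0.70 = 0.385, about 0.39 SD

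**4. Illustration: last available score (T2, else T1, else baseline).** The expected estimate is (proportion with T2) × (effect at T2) + (proportion with T1 but not T2) × 0.548. The assumed proportions missing at T1/T2 are 0%/0%, 10%/20% and 20%/30%.

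| Effect at 8 months | 0%/0% | 10%/20% | 20%/30% |
|---|---|---|---|
| Fully persists (0.548) | 0.55 | 0.49 | 0.44 |
| Halves (0.274) | 0.27 | 0.27 | 0.25 |
| Vanishes (0) | 0.00 | 0.05 | 0.05 |

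For example, the middle cell is 0.80 × 0.274 + 0.10 × 0.548 = 0.274. The 0%/0% column is also the 8-month reading with complete data. A simulation with 65 per arm, correlation 0.5 and non-differential drop-out agreed to within 0.01 SD. In the same simulation a baseline-adjusted T1 analysis of the observed scores, standing in for the two-moment mixed model, stayed at about 0.55 SD in every scenario.

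**The case against.** The strongest reply is that the primary analysis is already fixed. The Primary outcome and Primary outcome analysis sections give the population, the model, the two moments and the T1 contrast. The Secondary outcome sections place the 8-month scores elsewhere. One loose sentence stands against all of that, and within a two-moment model the last assessment is simply T1. The trial is also a proof of concept whose analyses are described as hypothesis-generating, and a separate analysis plan may be clearer.

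Much of this stands: the likely intent is the T1 mixed model. It does not remove the conflict. The sentence is a stated rule rather than a detail left for later, it is in the section an analyst would consult on missing data, and an 8-month visit exists that fits its words more literally than T1 does.

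Three stronger readings are tempting, and the document does not support them:

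- **That the ITT analysis will carry scores forward.** Carry-forward is never named, and the primary section specifies another method. It is one reading that the wording leaves open.
- **That the mixed model and missing at random are reserved for the per-protocol set.** The text does not say *only*. It refers to the model already proposed, and that proposal was made for the ITT analysis. The restriction is an inference from the ITT/PP contrast.
- **That measuring outcomes by patient report is impossible for the neuropsychological tests.** The sentence covers *key* secondary outcomes, a term the article does not define. Most listed secondary outcomes are self-reported, and nothing says the tests are among the key ones.

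A spurious difference from unequal drop-out is also a weak argument. With 10% against 25% drop-out and a common improvement of 0.4 SD, all assumed, carry-forward would create 0.4 × 0.15 = 0.06 SD. That is about a third of a standard error of √(2/65) = 0.175 SD.

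**Conclusion.** The concern holds as an internal contradiction in the current text. The missing-data section's rule for the ITT outcome does not agree with the two-month outcome, the mixed model for drop-out and the T1 contrast stated elsewhere, and it leaves the time point and the treatment of missing scores open to more than one reading.

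The size cannot be fixed from the article, because it gives neither a drop-out rate nor an expected course to 8 months. Under the assumptions shown, a 0.55 SD effect would become 0.50 to 0.39 SD if baseline were carried forward for 10% to 30% of patients. On the 8-month or last-available readings it would lie between about 0.00 and 0.55 SD, driven mainly by persistence of the effect. On the benign reading nothing changes. A reader should not conclude that the trial plans carry-forward or has changed its endpoint; the article establishes only that its sections disagree.

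**What to change.** Delete the *last assessment* sentence and replace the ITT and per-protocol statements in that section by text to this effect:

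- The ITT analysis includes all randomised patients as allocated and uses the linear mixed model of the primary analysis section, under missing at random.
- The contrast is at T1 for the primary outcomes, and at T1 and T2 for the secondary outcomes, as in the secondary analysis section.
- No value is carried forward.
- The per-protocol sensitivity analysis applies the same model to patients who completed the allocated treatment.

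Add one sentence on how the two-week repeat of BRIEF and MMQ enters the T1 score.

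The cost is a few sentences. Visits, data collection, N = 130 and the detectable f = 0.137 are unaffected.

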### Plans to give access to the full protocol, participant level-data and statistical code

The complete protocol is available on the KCE website. (https://kce.fgov.be/fr/kce-trials/essais-cliniques-finances). Data may be available upon reasonable request to the Principal Investigator.

## Oversight and monitoring

### Composition of the coordinating centre and trial steering committee

In summary, ULiège is the study Sponsor. [name] and [name] are the Chief Investigator (CI) and responsible for clinical elements of the trial. ULiège and UZA CTC are both responsible for project management. ULiège and UZA CTC will hold joint data controller responsibilities.

### Trial Steering Committee (TSC)

A TSC meets three times in the first year and twice in the second. The committee will provide overall supervision of the trial and ensure that the study is conducted according to the protocol and within the overarching ethical framework. It is composed of chief investigators, trial project manager, statistician, clinical experts (Chief of Internal Medicine and Chief of post intensive care Unit) of the coordinating centre; principal investigators of each participating centre, independent clinical expert (psychologist from University of Montreal); representative of UZA CTC; representative of the funder (KCE); two representatives of patients.

### Trial Management Group (TMG)

The TMG is the executive decision-making body and is responsible for the day-to-day running and management of the trial. It is led by the CIs and consists of representative of UZA CTC, representative of the funder, project manager and principal investigator from coordinating centre. The team meets each trimester (or more frequently if needed) via a teleconference to discuss clinical challenges and risks.

### Composition of the data monitoring committee, its role and reporting structure

Charter can be found, if not in the protocol. Alternatively, an explanation of why a DMC is not needed.

Data monitoring is under the responsibility of CTC UZA, that is independent from the sponsor and funder. A Clinical Monitoring Plan (CMP) was conjointly written by the CTC UZA, in collaboration with the chief investigators. The CMP establishes the guidelines for conducting monitoring visits and related tasks for monitoring protocol Long Covid. The CTC UZA will perform monitoring tasks in accordance with the protocol specific requirements. This plan aims to support the UZA monitor(s) to ensure that the investigational sites follow the International Conference on Harmonisation (ICH) Good Clinical Practice Guidelines (GCP), the local regulatory requirements and he study protocol.

### Adverse event reporting and harms

The project does involve interventions, but they are considered ‘low risk’ with no anticipated serious adverse events. Here, we should observe only mild adverse events related to the interventions, such as increased anxio-depressive affects in some patients when faced with cognitive difficulties. Such adverse events will be discussed with clinician and a trial safety group (composed of one principal investigator of the center, chief investigator, Trial Project Manager, one representative of patients) to determine the most appropriate response (e.g. mail to the general practitioner, psychological counselling outside of the intervention protocol). The date, description of the related adverse event, solution proposed will be recorded in the eCRF and in the source documentation (patient medical record). This information will be also transmitted to TSC.

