#### Concealment mechanism and Implementation

After the baseline session, an attribution request is then emailed, including the ID, to a researcher responsible for the attribution process with the QMinim software. This researcher does not participate in the follow-up assessment. This researcher then sets up the appointment with the clinician of the assigned arm.

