### Assignment of interventions: Blinding

#### Who will be blinded

The statistician will be blind to the content of the intervention arm that will be called “A” and “B”. The neuropsychologists who perform the baseline assessment do not know about the randomisation (which is only carried out after the visits). The neuropsychologists that will be in charge of follow-up will also be blinded to the arm of the intervention. Patients will be warned to not mention their intervention arm or provide information that could cue the clinician (this will be reminded before each assessment session). If the clinician becomes unblinded during the testing session, this will be reported in the eCRF.

The person administering the intervention cannot be blinded, as the content is different. The participants cannot be blinded. However, the trial will be presented as “assessing the positive effect of two interventions on post-covid cognitive difficulties” Our prediction (superiority of the cognitive intervention) will not be communicated to the participants until the end of the trial (last follow-up for the last participant included).

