#### Secondary outcome analysis

Mixed linear models will also be used to assess the maintenance of effect across time (baseline, immediate and long-term follow-up). We will re-run the same analysis as for primary outcome, this time by including scores at long-term follow-up. Intervention effect size will be estimated using the same mixed models for each secondary and exploratory outcome measurement (Scores of ISQV and EQ-5D, the 5 overall Z-score per cognitive domain, Outcome-Questionnaire 45, PSQI, M-FIS) at both short-term follow-up (T1) and long-term follow-up (T2). As a rule, stratification factors will be included in the analyses.

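### Adverse event recording is worded as limited to intervention-related events, with no named assessor of relatedness and no stated common way of asking, so counts could differ between arms through detection and attribution alone

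*Protocol article*

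**What the plan says.** The section on adverse event reporting and harms calls the interventions low risk, foresees no serious events, and adds: "Here, we should observe only mild adverse events related to the interventions". Its example is "increased anxio-depressive affects in some patients when faced with cognitive difficulties". On handling, it states: "Such adverse events will be discussed with clinician and a trial safety group". The group consists of a centre principal investigator, the chief investigator, the project manager and a patient representative, and its stated purpose is to choose a response. On recording, it states: "The date, description of the related adverse event, solution proposed will be recorded in the eCRF". The information also goes to the medical record and the steering committee.

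On allocation, the researcher who runs the minimisation knows the arm: "This researcher then sets up the appointment with the clinician of the assigned arm". On blinding: "The person administering the intervention cannot be blinded, as the content is different", and "The participants cannot be blinded". The neuropsychologists who do the follow-up assessments are blinded.

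Distress is also measured by the OQ-45, a self-report inventory scheduled for both arms before treatment and at 2 and 8 months after it. The secondary outcome analysis gives it a mixed-model effect size, in a list that ends "Outcome-Questionnaire 45, PSQI, M-FIS) at both short-term follow-up (T1) and long-term follow-up (T2").

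**The concern.** Two features of the wording combine. First, what enters the eCRF is the related event. The only antecedent in that paragraph is events related to the interventions, so the natural reading is a relatedness filter applied before anything is written down. An event taken to be unrelated would leave no record, and the judgement could not be audited or redone later.

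Second, nothing stated makes the filter the same in both arms. No relatedness assessor is named, no common question or contact is described, and the blinded assessors are given no role. Those who see the patient in the sessions know the arm and deliver different content. The risk that the protocol names is a mood change, and how readily it is noticed and attributed may depend on what the sessions discuss.

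The abstract says that the trial will show which usual type of intervention is more effective. A reader choosing between the two programmes will also look at the harms. If the counts partly reflect attribution, a real excess of worsening in one arm could be missed, or a false one created.

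**Working it through.** **Passages side by side.**

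| Question | What the article says |
|---|---|
| Which events are recorded? | The related event (adverse event section) |
| Who judges relatedness? | Not stated; the clinician and safety group choose the response |
| Are events elicited alike in both arms? | Not stated |
| Is the therapist blinded? | No, and the therapist is specific to the arm |
| Is the participant blinded? | No |
| Are follow-up assessors blinded? | Yes, with no stated adverse event role |
| Is distress measured alike in both arms? | Yes: OQ-45 at baseline, T1 and T2 |

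The article gives no adverse event rate, no OQ-45 worsening threshold and no worsening rate, so there is no harms figure of its own to reproduce. Its sensitivity figure (f = 0.137) concerns the primary outcomes and does not bear on this point. The arm size of 65 comes from the trial design section. Every rate below is an assumption.

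**1. Effect of unequal detection and attribution.** Recorded rate = true rate × share of true cases that are noticed and recorded as related.

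- True rate 15% in both arms: 0.15 × 65 = 9.75 patients per arm.
- Shares 80% and 40%: 0.15 × 0.80 = 12% (7.8 patients) versus 0.15 × 0.40 = 6% (3.9 patients), a twofold difference with no true one.
- Shares 70% and 50%: 10.5% versus 7.5% (6.8 versus 4.9 patients).
- True rate 10%, shares 80% and 40%: 8% versus 4%. True rate 20%, same shares: 16% versus 8%.

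Which arm has the higher share is left open. On the first set, 8 of 65 against 4 of 65 gives a Fisher p of 0.36 and a difference of 6 points (95% CI about −4 to 16). The distortion would usually not reach significance, but harms tables are read as counts.

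**2. What a mean comparison can leave unseen.** Suppose that both arms improve by 0.3 SD on average, with normally distributed changes of SD 1.0 in one arm and 1.5 in the other. The share worsening by more than 1 SD is Φ(−1.3/1.0) = 9.7% versus Φ(−1.3/1.5) = 19.3%. The means are equal, yet the share that worsens doubles. In a simpler case, 15% of one arm worsening by 1 SD is cancelled in the mean if the other 85% improve by 0.15/0.85 = 0.18 SD.

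**3. What an OQ-45 worsening table could show with 65 per arm** (two-sided alpha 0.05). For 10% versus 20%:

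- Pooled rate 0.15; null standard error √(0.15 × 0.85 × 2/65) = 0.0626; 1.96 × 0.0626 = 0.1228.
- Alternative standard error √((0.09 + 0.16)/65) = 0.0620.
- Power = Φ((0.10 − 0.1228)/0.0620) = 0.36. The 95% CI half-width is 1.96 × 0.0620, about 12 points.

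By the same formula, power is 0.62 for 10% versus 25% and 0.82 for 10% versus 30%. About 199 per arm would be needed for 80% power at 10% versus 20%. The table would be descriptive and could exclude only large differences.

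**The case against.** Several objections have force.

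- **Wording.** The phrase about the related event may be loose English for the event in question. That is possible. The filter is still the more natural reading, because the paragraph has just spoken of events related to the interventions.
- **Who judges.** A reader might infer that each arm's unblinded therapist decides relatedness. The article does not say so. The clinician and the safety group meet about the response, not about cause. The blinding section also uses the word clinician for the blinded tester, and the data management section has the evaluating clinician researchers enter eCRF data, so blinded entry is not ruled out. This stands: the defect is that the role is not assigned, not that it is assigned to the wrong person.
- **Direction.** A reader might infer that distress is seen more in the affective arm and missed in the cognitive arm. The affective modules do use emotion self-observation with a diary. But the cognitive arm opens with feedback on the patient's test results, addresses expectations of poor outcome and coping style, and aims to reassure. The direction and size of any gap are unknown.
- **Fair comparison of distress.** A reader might infer that the trial cannot compare distress at all. It can: the OQ-45 mixed model compares the randomised arms on the same schedule, although the reports come from unblinded participants.
- **Missing OQ-45 table.** The analysis plan and the full protocol are not shown, and such a table is ordinary content for them. Its absence here is not a fault; the table is offered as part of the remedy.
- **Stakes.** These are low-risk interventions in a hypothesis-generating trial, and the article announces no between-arm test of adverse events. That limits the weight of the point. It does not help anyone who later reads the counts by arm.

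**Conclusion.** The point holds in a limited form. Followed as written, the article restricts recording to related events, names no one to judge relatedness and describes no arm-neutral way of collecting events, while participants and therapists know the arm. Recorded counts would then depend partly on detection and attribution and would not be a sound basis for comparing harms. The size is not known. On assumed true rates of 10% to 20% and recording shares of 80% versus 40%, it would be a spurious twofold ratio, or 4 to 8 percentage points; at 70% versus 50% with a true rate of 15% it would be 3 points. The conclusion rests on reading the recording sentence as a relatedness filter. It does not claim that therapists judge relatedness, that a particular arm would be favoured, or that the planned OQ-45 analysis is wrong. The change is worth making during the trial, because unrecorded events cannot be reliably recovered afterwards.

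**What to change.** 1. State that every untoward event is recorded in both arms regardless of judged relatedness. Ask the same question at the same contacts in both arms, for example at the blinded T1 and T2 assessments.
2. Record relatedness as a separate field, and name who completes it and whether that person knows the arm.
3. Alongside the planned mixed-model mean comparison, add a descriptive by-arm table: the number and share of patients whose OQ-45 total worsened from baseline beyond a prespecified reliable-change margin, at T1 and at T2, with the difference and its 95% CI. If the unseen analysis plan already has this, a cross-reference is enough.

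The cost is a few more eCRF entries per patient, a longer list that includes unrelated events, and one extra table from data already planned. The table should be labelled descriptive because of its low power with 65 per arm. If all events are in fact already recorded, the fix for items 1 and 2 reduces to one clarifying sentence on recording and one on who assesses relatedness.
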